#### 2. Comprehensive assessment program (intervention group only)

After the randomization and an initial interview with the personal pilot, patients in the IG are assigned to a 3-day inpatient assessment. During the assessment, the functional capacity will be examined by different disciplines according to the bio-psycho-social model of the International Classification of Functioning (ICF) (DIMDI, 2005) and the need for treatment will be identified depending on the debilitating symptoms.

The 3-day inpatient assessment takes place in a specialized clinic (neurological-orthopedic stationary rehabilitation center). This clinic has the necessary (specialist) competence in the fields of neurology and orthopedics including physiotherapy, internal medicine, and psychology. The assessment aims to check in more detail and on basis of objective tests for the presence of PACS. Furthermore, the goal is to determine an individual interdisciplinary and cross-sectoral treatment plan, which can be translated into practice. This plan is then guided by the personal pilot in terms of empowering the patients to know about their symptoms, the recommended treatments, and what they can do themselves also by means of the digital training.

Concretely, the assessment is performed by means of physiological and psychological tests (see Table 2). These tests are based on the recommendations of the S1-guidelines (e.g., [17]) and consist also of a detailed medical history and review. From this, further individual assessments are derived adaptively. They are carried out by different therapists from the professional groups of pneumology, cardiology, internist, psychology, neurology, physiotherapy, occupational therapy, and nursing.

**Table 2 Tab2:** Diagnostic tools within the assessment

Domain	Parameter/ tests
Physical conditions and vital signs	• Height • Weight • Body fat • Pulse • Electrocardiography at rest • Oxygen saturation • Body temperature • Blood pressure • Breathing frequency
Lung	• Spirometry
Brain	• EEG • Initial neurological examination
Nerves	• Nerve conduction velocity • Somatosensory evoked potentials (SEP)
Stress test	• Schellong orthostasis test • Ergometry
Taste/smell	• Taste/smell tests (SS-16)
Psychological	• Attention test battery • Alertness test • California Verbal Learning test • Five Point test (divergent thinking) • Visual scanning test • Working memory test
Ability-to-act investigation	• Occupational therapy

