### Evaluation concept

A longitudinal randomized control trial design is used in this project with a three-group pretest–posttest procedure. Whereas the CompG will be recruited with different links via online invitations (e.g., via social media campaigns), the IG and the ACG are recruited with another separate link. After agreeing to take part in the study, participants will be randomized by throwing a dice. Patients for whom a 1 or 2 was rolled are placed in the IG and patients for whom a 3–6 was rolled are placed in the ACG. If a randomization cannot be realized (e.g., because they cannot take part in the stationary assessment due to organizational limitations), patients will be allocated to the ACG but will be marked for statistical analyses. Methodically, a propensity score matching will be used between the IG and the CompG to ensure the comparability of these groups (i.e., participants will statistically be matched by various person-related criteria such as age and sex). All groups are repeatedly interviewed with similar instruments in each group (see Table 1). Time points of measurement are the screening (T1), prior to the assessment in the IG and a comparable time point in the ACG (T2), after the assessment in the IG and at a comparable time point in the ACG (T3). Then approximately 6 weeks after T3 and after symptom-specific digital interventions, a further measurement will take place (T4). Another 6 weeks later a follow-up measurement will take place (T5). A last measurement time point (T6) will be conducted 6 months later with some selected participants. All time points of measurement are included in the study flow chart (Fig. 3).

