### Statistical analysis

#### Sample size planning

With an alpha error of 0.05 and a power of 68%, a sample of *N* = 132 (*n* = 66 in the IG and *n* = 66 in the ACG) is required to be able to demonstrate an effect of *d* = 0.15. The evaluation will be conducted statistically using a Multivariate Analysis of Variance (repeated-measures MANOVA: within-between interaction; power analysis calculated with G*Power). In addition to classical significance tests (*p*-value of a two-sided test below 0.05), the clinical significance will be calculated with effect sizes.

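### The deciding test is an omnibus group-by-time interaction with no primary time point or contrast, so a significant result need not reflect a difference at the post-intervention visits T4 and T5

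*Protocol article*

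**What the plan says.** **Schedule (Protocol article, Evaluation concept).** T1 is the screening and T2 precedes the IG assessment. The next measurement is "after the assessment in the IG and at a comparable time point in the ACG (T3"). The text continues: "Then approximately 6 weeks after T3 and after symptom-specific digital interventions, a further measurement will take place (T4"). T5 follows another six weeks later, and T6 is for selected participants only.

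**What lies between T2 and T3.** "The 3-day inpatient assessment takes place in a specialized clinic" (Comprehensive assessment program). Table 2 lists ergometry, an orthostasis test and a battery of cognitive tests. The ACG has no assessment. Under Study design and setting, both arms first get unspecific digital content, and the IG's individualised programme comes after the assessment.

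**Test.** Sample size planning names the analysis as "repeated-measures MANOVA: within-between interaction". Under the assessment and digital-therapy headings, Hypotheses 5 and 3 are tested by whether the groups differ in the development of symptoms, daily activities, RTW and participation, using MANOVA and repeated-measures ANOVA. The section on the type of analysis repeats this.

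**Endpoint.** The Evaluation concept gives symptom reduction and RTW as primary, without a time point. Outcomes come from questionnaires and/or interviews. The Blinding section says that participants, staff and evaluating researchers all know the allocation.

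**The concern.** An omnibus interaction rejects for any departure from parallel profiles, at any visit and in either direction. T3 is the first measurement after an inpatient stay that only one arm has, and it comes before the six-week programme interval. A reaction to that stay, upward or downward, is plausible for self-reported outcomes in an open trial.

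Two claims depend on where in the profile a difference sits. Hypothesis 3 attributes benefit to the individualisation of digital therapy. Hypothesis 5 says, among other things, that recovery is lasting. A difference present at T3 and gone by T4 and T5 supports neither, yet it can make the named test significant. With no contrast fixed in advance, researchers who know the allocation would decide afterwards which part of the profile the result is credited to.

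**Working it through.** **1. The plan's own figure.** Sample size planning states: "With an alpha error of 0.05 and a power of 68%, a sample of" 132 (66 per arm) "is required to be able to demonstrate an effect of *d* = 0.15". The G*Power form for a within-between interaction with two groups is λ = f²·N·m/(1−ρ), where m is the number of measurements and ρ their correlation. The article gives neither m nor ρ.
- f = 0.15, m = 2, ρ = 0: λ = 0.0225 × 132 × 2 = 5.94 on 1 and 130 df, power 67.7%. This matches the stated 68%.
- f = 0.15, m = 5, ρ = 0: λ = 14.85 on 4 and 127 df, power 87.4%.
- f = 0.075 (0.15 read as d, halved): 68% is reached at ρ of about 0.75 with m = 2, or about 0.61 with m = 5.

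The closest simple match is a two-measurement test, but the match is not unique. The visits in the test cannot be recovered from the power figure.

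**2. A difference at T3 only, if T1 to T5 all enter.** Inputs:
- From the article: two-sided alpha 0.05, and 66:66 from Sample size planning. The die rule in the Evaluation concept (1-2 to IG, 3-6 to ACG) gives about 44:88 of 132.
- Assumed: complete data, unit SD, equal correlation ρ between visits, and the T3 difference δ in SD.

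For five visits the squared distance between the change profiles is D² = 0.8·δ²/(1−ρ), and λ = D²·n₁n₂/(n₁+n₂). The last factor is 33 for 66:66 and 29.33 for 44:88. The test is F on 4 and 127 df, critical value 2.44. Example: δ = 0.3, ρ = 0.5, 66:66 gives D² = 0.8 × 0.09/0.5 = 0.144, λ = 4.75, rejection 36%.

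| δ at T3 | ρ = 0.3 (66:66 / 44:88) | ρ = 0.5 | ρ = 0.7 |
|---|---|---|---|
| 0.15 SD | 9% / 9% | 11% / 11% | 17% / 15% |
| 0.3 SD | 26% / 24% | 36% / 33% | 58% / 53% |
| 0.4 SD | 46% / 41% | 61% / 56% | 85% / 80% |

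The sign of δ does not matter. With autoregressive instead of equal correlation, the 0.3 SD range is 23-62%. With T3 left out, or with a single pre-post contrast such as T2 to T4, rejection is 5.0%. That follows by construction, because the assumed effect is then zero at every visit in the test.

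**3. Power for a sustained effect of 0.4 SD at T4 and T5, 66 per arm.**
- Omnibus: D² = 1.2 × 0.16/(1−ρ). ρ = 0.5: λ = 33 × 0.384 = 12.67, power 81%. ρ = 0.7: λ = 33 × 0.64 = 21.12, power 97%.
- Mean of T4 and T5 adjusted for T1: residual variance (1+ρ)/2 − ρ², F on 1 and 129 df. ρ = 0.5: λ = 33 × 0.16/0.50 = 10.56, power 90%. ρ = 0.7: λ = 33 × 0.16/0.36 = 14.67, power 97%.
- T5 alone adjusted for T1: residual variance 1 − ρ². ρ = 0.5: λ = 33 × 0.16/0.75 = 7.04, power 75%. ρ = 0.7: λ = 33 × 0.16/0.51 = 10.35, power 89%.

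All of this is for a continuous symptom score. Nothing was computed for RTW.

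**The case against.** **Which visits enter may be settled elsewhere.** The article condenses a fuller document, calls the design a pre-post procedure, and gives a power figure that fits two measurements best. If one pre-post pair is tested and T3 is not in it, the problem disappears. This stands as far as it goes: a reader might infer that T3 carries full weight in the primary test, and the text does not say so. It says only enough to show that T3 is not excluded. But the article does fix an interaction test as the deciding one, lists five visits for the full sample, and gives no pair. Naming the contrast is the remedy on either reading.

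**T3 is not outside treatment.** A reader might infer that a T3 difference is a false positive. The text does not support this. The assessment is one of the four evaluated components, it is tied to Hypothesis 5, and prescriptions and recommendations are made at discharge from it. A T3 difference between randomised arms is a real effect of the IG strategy. It misleads only if credited to digital individualisation or to lasting recovery.

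**Timing and direction.** The article says that T3 comes after the assessment, not how soon, so an argument from immediate exertion goes beyond it. The omnibus test has no direction, and a T3-only pattern would show in the profile by visit. Both points stand. The second still leaves the reading of the profile unspecified in advance.

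**Size.** The larger T3 effects are assumed and exceed the planned 0.15 if that is a d. At 0.15 SD rejection is only 9-17%. This stands.

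**Conclusion.** The concern holds in a limited form. The article lets an undirected interaction decide Hypotheses 3 and 5 without a primary time point or contrast, so significance alone would not establish a difference at T4 or T5. If T1 to T5 all enter, a T3-only difference triggers the test in 9-17% of trials at 0.15 SD, 24-58% at 0.3 SD and 41-85% at 0.4 SD. These ranges rest on assumed effect sizes, equal correlations of 0.3 to 0.7, complete data and a continuous outcome. The documents do not establish that T3 is in the test, that it is taken immediately after the stay, or that an effect there is spurious. The point is worth correcting because the claims concern individualised digital care and lasting recovery, and the remedy is cheap.

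**What to change.** Pre-specify one IG-ACG contrast after the intervention as the deciding test for symptoms, adjusted for the T1 value. The mean of T4 and T5 is preferable; T5 alone is an alternative. Use RTW status at T5. Report T2, T3 and the full group-by-time profile as secondary information on the early effect of the assessment, and state which visits enter each model.

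The cost is wording in the Evaluation concept and the Statistical analysis section, with no new visits or data. A difference present at T3 only would no longer count as success. For the sustained effect examined above, the T4/T5 mean loses no power against the omnibus test. T5 alone loses 6 to 8 percentage points (81% to 75%; 97% to 89%), which matters in a trial planned at 68%.

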### Diagnosis of the post-acute COVID-19 syndrome

A possible complication or long-term consequence of acute COVID-19 is the occurrence of the post-acute COVID-19 syndrome (PACS, which can be used as synonym for long- and post-COVID) [3]. There are conservative estimates that 4 weeks after the onset of acute COVID-19, about 10% of patients still suffer from symptoms that warrant the diagnosis of post-acute COVID-19 syndrome  [12]. Since there are many different symptoms, this complex diagnosis requires reliable and valid diagnostics for comprehensive symptom clarification, and carefully planned, individual treatment afterwards. Due to the interdisciplinary symptomatology, there is currently no uniform care structure in Germany. Hence, affected patients are mainly treated separately and sequentially by general practitioners and specialists which leads to long waiting times. However, there is no holistic control of a thoroughly necessary intersectoral therapy.

In contrast to the acute infection, there are currently no validated, uniform diagnostic criteria, so that the development and further refinement of scientific evidence for research into this clinical diagnosis is required [13] and the diagnosis of PACS is made as a clinical case definition, that is, in the presence of symptoms like the ones in Fig. 1 depicted.

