### The Research Project

The objective of the present study is the early detection of post-acute COVID-19 symptoms (PACS) and subsequently a long-term and sustainable holistic care and support of patients with PACS to avoid long-term illness and chronification, and to enable social participation.

The long-term goals of the study are the dissemination of validated instruments (i.e.g., the online screening) and newly developed treatment approaches (i.e., the digital interventions and a  personal pilot concept) through communication to central stakeholders such as medical associations, health insurance companies, service providers in the outpatient and inpatient sector as well as professional societies and care institutions. In this way, patient care is to be improved beyond the project duration and care services are to be made more efficient.

Hypotheses, which will be tested with this project, are the following:A short *screening* can detect the presence of PACS.A comprehensive* assessment* can validly and reliably determine rehabilitation or remedial needs and the leading rehabilitation indication and be basis of an individual multidisciplinary treatment plan.The more *individualization* the digital therapy offers, the higher the effectiveness in the treatment of PACS.As contact point for all involved parties, a *personal pilot * empowering the patient suffering from PACS can -by means of an interdisciplinary and intersectoral treatment planning- ensure the sustainable management of interdisciplinary treatment.An *interdisciplinary treatment pathway* and the personal pilots empower the patients, so that the patients receive the appropriate diagnosis and treatment, and to actively participate in their own recovery, ensuring patients recover quickly and sustainably from their PACS conditions, increase their functional capacity, reduce incapacity to work and regain participation.

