Internal diagnostics	• Echography • Carotis-duplex sonography

The results of the assessment for each professional group will be handed to a clinician, who is then able to make a holistic assessment of whether PACS is present or not. These assessments are also summarized to form a holistic treatment plan, which synopsizes the findings and lists the indicated medical and therapeutic measures. These recommendations will be made visible for the personal pilot, and subsequently made available to the attending outpatient doctor.

The prescription of necessary treatments and aids, as well as the recommendation of digital interventions already take place within the framework of discharge management. If the need for a rehabilitation measure is determined, this will be communicated to the patient directly in a way to enable him/her applying for rehabilitation treatment and finding the most appropriate treatment within Germany (also with the help of the personal pilot).

Using such an approach allows us to test Hypothesis 2, that a comprehensive assessment can determine rehabilitation or remedial needs and the leading rehabilitation indication. To assess the applicability of this hypothesis, we will consider a comparison of test–retest reliabilities of the degree of experienced symptoms in the IG compared with the ACG and the CompG. Furthermore, the assessment allows us also to test Hypothesis 5 that an interdisciplinary treatment pathway empowers the patient. To assess the applicability of this hypothesis we will check whether IG, ACG and CompG differ in terms of the development of symptoms, increased activities of daily lives, RTW and increased social participation. To do so, we will consider MANOVA and repeated measurement ANOVA analyses.

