For the *summative effectiveness evaluation*, the primary endpoint is the symptom reduction regarding PACS, and RTW. Secondary outcomes include social participation, health-promoting behaviors, and activities of daily living (ADL) as well as mental health and life satisfaction/quality of life. Survey and documentation of all endpoints are conducted by means of questionnaires and/or interviews with study participants who have completed interventions over the course of the project as described above. In addition, possible moderators (especially socio-demographic data) and mediators (e.g., motivation, self-efficacy, and coping strategies) are quantitatively reviewed and added to the analyses. An overview of the measures is provided in Table 2 and Additional file 1.

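### Measurements on all patients stop about 12 weeks after T3, so the randomised comparison cannot support the sustained-recovery, durable return-to-work and chronification claims

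*Protocol article*

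**What the plan says.** The schedule is in the protocol article under Evaluation concept. T3 follows the 3-day assessment in the IG and is set at a comparable time in the ACG. After that:

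- T4: "Then approximately 6 weeks after T3 and after symptom-specific digital interventions, a further measurement will take place (T4".
- T5: "Another 6 weeks later a follow-up measurement will take place (T5".
- T6: "A last measurement time point (T6) will be conducted 6 months later with some selected participants".

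The same section states that "the primary endpoint is the symptom reduction regarding PACS, and RTW". No time point is attached to either component.

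The Research Project gives the objective as early detection followed by "long-term and sustainable holistic care and support of patients with PACS to avoid long-term illness and chronification". Hypothesis 5, in the same section, expects recovery that is both quick and sustainable, together with less incapacity to work.

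On rehabilitation, Study design and setting lists its initiation among several possible recommendations from the IG assessment. The section on the comprehensive assessment makes it conditional on a determined need, which is then communicated to the patient "to enable him/her applying for rehabilitation treatment and finding the most appropriate treatment within Germany". Digital therapy offers expects IG patients to wait for the assessment and for other therapies, without giving a length. The Personal pilot section has pilots support referral to rehabilitation in both the IG and the ACG.

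**The concern.** The claims reach further in time than the data. Words such as long-term, sustainable and chronification concern what happens after the first gain. As written, the only measurement after T5 is restricted to a subset. No later analysis plan can recover T6 data that were never requested from the rest of the randomised patients.

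A positive T5 result could then be reported as sustained recovery without evidence that it lasted. T6 findings from a selected subset could be read as if they were a randomised comparison. Unless the subset is drawn at random within each arm, which the article does not say, patients chosen after randomisation may differ between arms, and the comparison loses the protection that randomisation gave it.

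There is a second, weaker point about RTW. Rehabilitation arranged after the assessment may be pending or under way at T5. RTW at that visit would then precede the completion of a treatment that the Background section links to restoring workability.

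**Working it through.** **1. Timeline.** Inputs are from Evaluation concept.

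- T4 = T3 + 6 weeks.
- T5 = T4 + 6 = T3 + 12 weeks.
- T6, if counted from T5 and taking 6 months as 26 weeks: 12 + 26 = 38 weeks after T3. If counted from T3 instead, about 26 weeks.

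Full-sample follow-up after T3 is therefore 12 weeks. With T6 in everyone it would be 26 to 38 weeks, and 38 is the more natural reading because the neighbouring intervals each run from the previous visit.

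**2. Claims set against the data.**

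| Claim | Latest data in all patients | Supported? |
|---|---|---|
| Quick recovery, short-term RTW | T4 and T5, 6 and 12 weeks | Yes |
| Sustained recovery | T5, 12 weeks | No |
| Durable reduction of incapacity to work | T5, 12 weeks | No |
| Avoiding long-term illness and chronification | T5, 12 weeks | No, beyond persistence at T5 itself |

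**3. How far unfinished rehabilitation could move RTW at T5.** The document gives no RTW rate, referral share, wait or duration, so this is an illustration on assumed values. Assume RTW of 70% in the IG and 50% in the ACG when nobody is in or awaiting rehabilitation, with 66 per arm as in Sample size planning. Let s be the share of an arm in or awaiting rehabilitation at T5, and r the RTW rate among them.

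Observed rate = p(1 − s) + r·s, where p is the arm's rate without rehabilitation. Power is the two-sided 5% normal approximation for two proportions with pooled variance under the null, Φ(z), where z = [|Δ| − 1.96·√(2p̄(1 − p̄)/n)] / √([p₁(1 − p₁) + p₂(1 − p₂)]/n).

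| IG s | ACG s | r | IG observed | ACG observed | Difference | Power |
|---|---|---|---|---|---|---|
| 0 | 0 | – | 0.70 | 0.50 | +20 points | 0.65 |
| 0.20 | 0 | 0.5 | 0.70×0.80 + 0.5×0.20 = 0.66 | 0.50 | +16 | 0.46 |
| 0.20 | 0 | 0 | 0.70×0.80 = 0.56 | 0.50 | +6 | 0.10 |
| 0.20 | 0.20 | 0 | 0.56 | 0.50×0.80 = 0.40 | +16 | not computed |
| 0.10 | 0.20 | 0 | 0.70×0.90 = 0.63 | 0.40 | +23 | not computed |

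Against the starting +20 points, the 12-week difference moves anywhere from −14 to +3 points in these rows alone. The sign depends on which arm has more patients in rehabilitation and on whether they work meanwhile. The document fixes neither.

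**The case against.** Several points on the other side stand.

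- T4 and T5 fit what the trial itself delivers after T3. T4 is timed to follow the digital interventions, and 12-week data do address the quick part of Hypothesis 5 and short-term RTW. A reader might infer that T5 cannot answer the RTW question at all. That goes too far: RTW is given no fixed time point, and early RTW is a legitimate result.
- A reader might also infer that IG patients in rehabilitation are scored as not returned and that T5 is therefore biased against the IG. Nothing shown says how RTW is scored, and Additional file 1 is not at hand. Pilots support rehabilitation referral in both arms. Patients who are waiting may still be working.
- The remark that "affected patients are mainly treated separately and sequentially by general practitioners and specialists which leads to long waiting times" describes existing German care, which the pathway is meant to improve. It does not show that waits within the trial exceed 12 weeks.
- If rehabilitation does postpone return, a lower 12-week RTW rate is a true effect of assignment at that time. Preferring a later time point is then a choice of estimand.
- On the NICE terms reported in the Background, symptoms beyond 12 weeks already count as post or chronic COVID-19. T5 lies at least 4 + 12 = 16 weeks after the infection, so persistence at T5 says something about chronicity in that narrow sense.

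None of this supplies evidence that a gain seen at T5 lasts. The objection removes any stated size or direction for the rehabilitation effect and leaves the gap in follow-up untouched.

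**Conclusion.** The point holds as a mismatch between claim and schedule. The randomised IG–ACG comparison has no full-sample data beyond about 12 weeks after T3, while the objective and Hypothesis 5 claim sustained recovery, less incapacity to work and avoidance of chronification. This rests only on the stated intervals and on the restriction of T6 to a subset. It would remain with complete data at T4 and T5.

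The rehabilitation point is a caution only: RTW at T5 may be read before recommended rehabilitation is finished, in either arm. It is tempting to put a figure on it. For example, one could assume that 30–50% of the IG are referred and half of those are still waiting or away (15–25%), subtract an assumed 5–10% in the ACG, and arrive at 5 to 20 points against the IG. Every one of those inputs is an assumption. The calculation also treats each affected patient as someone who would otherwise have returned. The document supports neither the size nor the sign.

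This is a cheap and worthwhile improvement. The short-term results are not invalidated by it.

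**What to change.** Send the T6 online questionnaire to all randomised IG and ACG patients. State the visit from which its 6 months are counted. Base the conclusions on sustainability, chronification and durable RTW on that full-sample comparison, and keep T4 and T5 as short-term results.

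If T6 has to remain a selected subset, label it descriptive and limit the RTW and Hypothesis 5 conclusions to about 12 weeks after T3, without the word *sustainably*.

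The first option costs one more online questionnaire and reminder for each patient not already selected for T6, and a later final read-out. The platform and the time point already exist. The second option costs wording only. Neither changes patient care.
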